# Bipolar haemostatic forceps versus standard therapy by haemoclip + / − epinephrine injection as initial endoscopic treatment in active non-variceal upper GI bleeding: study protocol for a prospective, randomized multicentre trial (BeBop-Trial)

**DOI:** 10.1186/s13063-023-07394-x

**Published:** 2023-06-15

**Keywords:** Haemostasis, Endoscopic, Gastrointestinal haemorrhage, Randomized controlled trial

## Abstract

**Background:**

Patients with active nonvariceal upper gastrointestinal bleeding (NVUGIB) usually require urgent endoscopic treatment. Standard therapy (ST) using haemoclip + / − epinephrine injection is not always successful. Bipolar haemostatic forceps (HemoStat/Pentax®) are an approved medical device for the treatment of gastrointestinal bleeding. However, their use as a primary endoscopic treatment for active NVUGIB has not yet been proven in a randomized prospective study.

**Methods:**

This is a prospective, randomized, multicentre superiority trial (*n* ≥ 5). Patients with active NVUGIB will be randomized (1:1) to ST and to experimental therapy (ET) by application of bipolar haemostatic forceps.

In the case of failed initial treatment within 15 min, crossover treatment will be attempted first. Rescue treatment (e.g. via over-the-scope-clip) will then be allowed after 30 min. All patients will also receive standard therapy with proton pump inhibitors. Forty-five patients per treatment arm are required to demonstrate an absolute difference of 25.4% with a power of 80% and a significance level of 0.05.

**Discussion:**

The hypothesis of the study is that bipolar haemostatic forceps are superior to ST in terms of successful primary haemostasis and the absence of recurrent bleeding within 30 days (combined endpoint). The 1:1 randomization is also ethically justifiable for this study, as both procedures are approved for the intervention in question. To further increase the safety of the patients in the study, crossover treatment and rescue treatment are planned. The prospective design seems feasible in a reasonable time frame (recruitment period of 12 months), as nonvariceal upper gastrointestinal bleeding is common. Anticoagulants and/or antiplatelet drugs could be an important confounding factor in the statistical analysis that needs to be taken into account and calculated if necessary. In conclusion, this randomized, prospective, multicentre study could make an important contribution to answering the question of whether bipolar haemostatic forceps could be the first-line therapy in the endoscopic treatment of stage Forrest I a + b NVUGIB.

**Trial registration:**

ClinicalTrials.gov NCT05353062. Registered on April 30 2022.

**Supplementary Information:**

The online version contains supplementary material available at 10.1186/s13063-023-07394-x.

## Introduction

### Background and rationale {6a}

The most common causes of acute upper gastrointestinal bleeding are nonvariceal. These include gastric and duodenal ulcers, erosive mucosal diseases of the oesophagus, stomach or duodenum, malignant diseases, Mallory-Weiss syndrome, Dieulafoy lesions, unidentifiable causes [1], or bleeding after endoscopic interventions such as polypectomy, endoscopic mucosal resection (EMR), or endoscopic submucosal dissection (ESD) [2].

The European Society of Gastrointestinal Endoscopy (ESGE) recommends a combination of thermal or mechanical therapy + / − epinephrine injection for patients with actively bleeding ulcers (Forrest I a and I b) in the updated guidelines on nonvariceal upper gastrointestinal bleeding published in 2021 [3]. Usually, a haemoclip is used as mechanical therapy. According to the GRADE criteria (Grading of Recommendations, Assessment, Development and Evaluation [4], the level of recommendation is strong and based on high-quality scientific evidence. However, as these methods are sometimes insufficiently effective in high-risk situations, the guideline recommends the use of an over-the-scope clip (OTSC) for actively bleeding ulcers > 2 cm in size that have a large visible vessel > 2 mm or are in a high-risk vascular location (e.g. gastroduodenal or left gastric artery), or for excavated/fibrotic ulcers, although no prospective randomized studies are available [3]. The most recently published studies on thermal haemostasis have predominantly used monopolar haemostatic forceps [5–8]. However, all these studies also included ulcers that were not actively bleeding (Forrest II and/or Forrest II b), which reduces the clear definition of the efficacy of the respective haemostatic method, as not all ulcers in stage Forrest II a or b bleed again. Only in a small, nonrandomized study of 50 patients was the use of bipolar haemostatic forceps more effective than endoscopic clipping in terms of initial haemostasis. However, no statistical superiority was shown in the prevention of recurrent bleeding [9]. Nonbleeding ulcers in stage Forrest II a and tumour bleeding, which often cannot be satisfactorily treated endoscopically, were also included. The bipolar haemostatic forceps from Pentax [10] has already been approved for the treatment of bleeding in the gastrointestinal tract in Europe as well as in Germany. Moreover, it has been successfully used to treat blood vessels or active bleeding during endoscopic submucosal dissection (ESD) and third-space endoscopy, such as peroral endoscopic myotomy (POEM). In contrast to monopolar forceps, there is no need to attach an earthing cable to the patient, as the current flow is directly between the opened branches of the forceps and not through the entire body. This also prevents electrical interference with implanted pacemakers or cardioverter defibrillators. Furthermore, only superficial tissue layers are destroyed by the horizontal current flow, which might reduce the risk of perforation. In summary, there is an unmet need for an easy-to-use and safe haemostasis method that achieves a very high initial haemostasis rate, prevents rebleeding in the long term, and can be used in all sites that can be reached with conventional oesophagogastroduodenoscopy. Pentax bipolar haemostatic forceps may offer a solution to this need. Its use has not yet been demonstrated in a prospective randomized study with a statistically sufficient number of patients.

### Objectives {7}

The efficacy and safety of bipolar haemostatic forceps should be investigated in the primary treatment of active, nonvariceal upper gastrointestinal haemorrhage of any cause (except tumour haemorrhage) in a randomized, prospective, multicentre superiority trial. In this setting, bipolar haemostatic forceps are the experimental study arm, and the standard therapy of haemoclip + / − epinephrine injection is the comparator study arm. The primary objective is the combined endpoint of successful initial endoscopic haemostasis and the absence of rebleeding within 30 days after successful initial haemostasis. Secondary objectives are the number of salvage procedures such as OTSC, angiography + coiling or surgery for primary haemostasis, type and number of therapy-associated complications, number of endoscopic reinterventions in 30-day intervals, number of blood units transfused, length of hospital stay, length of intensive care unit stay, and 30-day mortality.

### Trial design {8}

The trial design is as follows: prospective, multicentre superiority trial with 1:1 randomization of standard therapy versus experimental therapy.

## Methods: participants, interventions, and outcomes

### Study setting {9}

At least five study centres in Germany are participating. The study centres consist of university hospitals as well as community hospitals. The coordinating study centre is Helios Kliniken Schwerin, the university campus of Medical School Hamburg. The actual study centre list is available at the coordinating study centre study centre on request.

### Eligibility criteria {10}

Inclusion criteria:Age ≥ 18 yearsActive, nonvariceal upper gastrointestinal haemorrhage in the oesophagus, stomach, or duodenum (including metachronous, postinterventional haemorrhage): Forrest I a bleeding = spurting or pulsatile bleeding or Forrest I b bleeding = oozing bleedingWritten consent of the patient or available authorized surrogateLife expectancy of at least 30 days

Exclusion criteria:Nonactive, nonvariceal upper gastrointestinal bleeding stage Forrest II a-c or Forrest III (ulcer)Variceal haemorrhage = bleeding from varices in the oesophagus, stomach, or duodenumTumour haemorrhageSevere coagulation disorder not responding to transfusion of blood products: platelet count < 50.000/μl and/or INR > 3.0 and/or PTT > 2 × the normal value (> 52–72 s depending on reagent)Emergency that precludes endoscopy (for example, perforation in the gastrointestinal tract)Pregnant or breastfeeding patient

Only gastrointestinal endoscopists with more than 5 years of experience in emergency endoscopy who are familiar with both methods of haemostasis may perform the study therapy.

### Who will take informed consent? {26a}

Informed consent from potential trial participants or authorized surrogates will be obtained by the investigator before application of the study therapy.

### Additional consent provisions for collection and use of participant data and biological specimens {26b}

N/A. Additional collection and use of participant data for other reasons as well as collection of biological specimens are not provided.

## Interventions

### Explanation for the choice of comparators {6b}

The European Society of Gastrointestinal Endoscopy (ESGE) recommends a combination of thermal or mechanical therapy + / − epinephrine injection for patients with actively bleeding ulcers (Forrest I a and I b) in the updated guidelines on nonvariceal upper gastrointestinal bleeding published in 2021 [3]. Therefore, haemoclip + / − epinephrine injection is used as a comparator.

## Intervention description {11a}

### Standard intervention

The bleeding vessel is clamped with a clip, which remains in the patient. Since clips from different manufacturers (Boston®, Cook®, MICRO TECH® and others) are largely equally effective, the use of a specific product is not intended in the study. In most cases, the clip falls off spontaneously after a few days and is later excreted with bowel movements. Injection with adrenaline solution at a dosage of 1:10,000 in 10 ml (= adrenaline 0.1 mg/ml) can produce an additive effect on haemostasis by vasoconstriction and by “cushion” vascular compression. Its use is optional.

### Experimental intervention

Bipolar haemostatic forceps are placed directly on the bleeding vessel with the forceps open, and current is applied, flowing between the open forceps arms. The current application is triggered by the examiner via a foot pedal that is connected to the generator. The current is applied with short pulses of a few seconds until haemostasis is complete.

The HemoStat-WideCup bipolar haemostatic forceps from Pentax Medical (Fig. 1) [10] is a therapeutic medical device already certified for use in the gastrointestinal tract.

**Fig. 1 Fig1:**
[figure not shown]
Pentax HemoStat-WideCup bipolar haemostatic forceps inserted in the endoscope (left) and shown as a whole catheter (right)

The settings on the connected current generator may differ. The manufacturer recommends the following settings, which can also be saved as a separate setting programme in the generator if necessary (Fig. 2). The settings may be modified by the user. Bipolar electric forceps must not be used in the direct vicinity of flammable gases, liquids, or substances with a risk of fire or explosion, which does not occur in the body during regular use.

**Fig. 2 Fig2:**
[figure not shown]
Settings of the HemoStat WideCup bipolar electric haemostatic forceps for different generators

Both experimental therapy (ET) and standard therapy (ST) are used primarily with the aim of stopping bleeding within a period of 15 min after locating the source of bleeding.

### Criteria for discontinuing or modifying allocated interventions {11b}

If no haemostasis is achieved, it should be attempted in the following 15 min with the opposite method (ET after ST or ST after ET) (= crossover treatment). If no haemostasis is achieved after a total time of approximately 30 min, alternative haemostasis methods such as topical haemostatic spray/powder, over-the-scope clip, angiographic coiling, or surgery can be used (= rescue treatment).

### Strategies to improve adherence to interventions {11c}

The investigator will check daily during the hospital stay as to whether coagulation medication has been started and discontinued according to the guidelines. He will also check daily to determine whether the proton pump inhibitors prescribed in the study protocol have been taken. At the follow-up examination after 30 days, the patient will be asked whether the prescribed proton pump inhibitors have been taken. Moreover, the patient will be informed that taking proton pump inhibitors is important to fulfil the criteria of the study protocol.

### Relevant concomitant care permitted or prohibited during the trial {11d}

All patients with suspected nonvariceal upper gastrointestinal bleeding will receive an intravenous bolus of the proton pump inhibitor pantoprazole 80 mg prior to the endoscopic examination according to the guidelines, followed by an intravenous bolus or short infusion of 40 mg/day 3 times a day or continuous intravenous administration with a dosage of 240 mg pantoprazole/day for 3 days. In the case of ulcer bleeding, the proton pump inhibitor pantoprazole 40 mg orally in tablet form will be continued at a dosage of 1-0-1/day for the entire follow-up period of 30 days (or beyond, depending on the requirements of the treating physician).

Discontinuation and resumption of anticoagulant medication will be conducted according to the guidelines of the European Society of Gastrointestinal Endoscopy (ESGE) [12]. As a rule, medication with an anticoagulant drug should be resumed no later than 48 h after successful haemostasis if the indication persists. The procedure for exceptions to this rule, for example, in the presence of mechanical heart valves, can be found in the guideline. The anticoagulant medication will be carefully documented over the entire examination period from the initial emergency endoscopy to the end of the follow-up period after 30 days.

### Provisions for post-trial care {30}

N/A as ancillary and post-trial care are not planned, and additional assurance for trial participation is not necessary, as both therapies are approved.

### Outcomes {12}

All efficacy and safety parameters will be documented in a case report form (CRF) developed for the study.

#### Primary outcome measure

Success of primary haemostasisPeriod: 15 min from localization of the source of bleeding until haemostasisMethod of measurement: assessment by endoscopist: yes/noExplanation: variable of immediate effectivenessNumber of recurrent haemorrhages within 30 daysPeriod: 30 days after initial haemostasisMethod of measurement: evidence of recurrent gastrointestinal bleeding on oesophagogastroduodenoscopy or clinical signs of upper gastrointestinal bleeding (such as tarry stools) and an associated drop in haemoglobin of > 1 g/dl or 0.62 mmol/lExplanation: variable of sustained efficacy in an appropriate observation period, as recurrent bleeding is not uncommon after endoscopic haemostasis

#### Secondary and other outcomes

Type and number of therapy-associated adverse eventsPeriod: 30 daysMeasurement method: description and countExplanation: parameters of safety of haemostasis methodsNumber and success of crossover treatmentPeriod: 30 min after localization of the source of bleedingMeasurement method: counting and assessment by the endoscopist: yes/noExplanation: further method to assess the efficacy of the haemostasis intervention with due regard to patient safetyType, number, and success of rescue treatmentPeriod: up to 6 h after localization of the source of bleedingMethod of measurement: assessment, counting and evaluation by the investigator: yes/noExplanation: Further method to assess the efficacy of the haemostasis intervention with due regard to patient safetyNumber of endoscopic reinterventionsPeriod: 30 days after initial successful endoscopic haemostasisMeasurement method: count of further endoscopic haemostasis procedures performedExplanation: indirect test of the effectiveness of the primary haemostasis methodNumber of blood units transfusedPeriod: 30 days after successful initial haemostasisMethod of measurement: count of infused blood units (transfusion unit) per patientExplanation: indirect test of the effectiveness of the primary haemostasis methodLength of hospital stayPeriod: 30 days after successful initial haemostasisMeasurement method: count of hospital days rounded up to the nearest whole dayRationale: indirect assessment of the effectiveness of the primary haemostasis methodLength of the intensive care unit (ICU) stayPeriod: 30 days after successful initial haemostasisMethod of measurement: count of the ICU days rounded up to the nearest whole dayExplanation: indirect test of the effectiveness of the primary haemostasis method30-day mortalityPeriod: 30 days after successful initial haemostasisMethod of measurement: count of patients who die during the interval, regardless of the cause of deathExplanation: indirect test of the effectiveness of the primary haemostasis methodTime until reaching complete initial haemostasisPeriod: 15 min after starting initial haemostasisMethod of measurement: time measurement in minutesExplanation: indirect test of the effectiveness of the primary haemostasis method

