**Table 1 Tab1:**
[figure not shown]
Participant timeline. Haemoclip + / − epinephrine injection and bipolar haemostatic forceps are only used as crossover treatment if successful haemostasis has not been achieved after 15 min (X). Rescue therapy (OTSC, coiling, surgery) is only applied if successful haemostasis has not been achieved after a further 15 min by crossover treatment (X)

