### Adverse event reporting and harms {22}

Adverse events (AEs) will be documented at the start of oral endoscope insertion and will end 30 days after the first haemostatic procedure. The type and number of adverse events are secondary outcome variables as defined above. Subsequent adverse events may no longer be directly related to details of the study or procedure. Overall, adverse events attributable to ST or ET are expected to be rare [3, 9]. An adverse event is defined as a serious adverse event (SAE) if it is fatal, life-threatening, or results in permanent or severe disability or incapacity. If an adverse event is classified as serious, it will be documented on a separate SAE form in addition to the AE documentation in the CRF. Patients will be asked at the 30-day query if any adverse or serious adverse events occurred. Adverse events will be documented in the CRF with the following parameters: date and time of occurrence and cessation, association with trial therapy, and outcome of the adverse event. Conditions that existed prior to the administration of the investigational product will be documented not as adverse events but as concomitant conditions. Any new disease or any disease that increases in severity during the trial shall be documented as an adverse event. Each adverse event shall be assessed by the investigator as to whether a relationship to the intervention can be suspected. The nature and pattern of the reaction, the temporal relationship with the intervention, the clinical condition of the patient, concomitant medication, and other relevant clinical parameters should be considered. If the event occurs due to lack of efficacy or due to the underlying disease, it shall be considered independent.

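### Coiling or surgery for a rebleed after the 6-hour rescue window enters no procedure count, so a rebleed sent straight to either scores zero reinterventions

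*Protocol article*

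**What the plan says.** Apart from crossover treatment, the protocol article defines two procedure counts under *Secondary and other outcomes*.

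- **Rescue treatment** (type, number and success). The period is "up to 6 h after localization of the source of" bleeding.
- **Endoscopic reinterventions**, over 30 days from initial successful endoscopic haemostasis. The measurement method is a "count of further endoscopic haemostasis procedures", and the stated purpose is an indirect test of how effective the primary method is.

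Rescue is defined in *Criteria for discontinuing or modifying allocated interventions {11b}*: "If no haemostasis is achieved after a total time of approximately 30 min, alternative haemostasis methods" may be used, with coiling and surgery among the examples. The Table 1 legend agrees: "Rescue therapy (OTSC, coiling, surgery) is only applied if successful haemostasis has not been achieved after a further 15 min by crossover treatment". Rescue is thus the step after failed initial and crossover treatment of the index bleed.

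*Objectives {7}* draws the same lines. It lists the "number of salvage procedures such as OTSC, angiography + coiling or surgery for primary haemostasis" and, separately, the "number of endoscopic reinterventions in 30-day intervals".

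**The concern.** The two counts do not meet. Rescue covers coiling and surgery but belongs to the index bleed and stops at 6 hours. The 30-day count covers the later period but admits endoscopic procedures only. A patient who rebleeds on, say, day 4 and goes directly to coiling or surgery adds nothing to either.

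This matters because coiling and surgery are alternatives to repeat endoscopy. When one replaces the other, a count restricted to endoscopy falls as the course gets worse. An outcome meant to reflect the effectiveness of the first method then gives the better score to the worse result, and no outcome shows by arm how often a rebleed needed embolisation or surgery. Ward physicians know the allocation (*Who will be blinded {17a}*), so the route chosen for a rebleed could differ by arm, and with it the number left out.

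**Working it through.** **1. Which outcome counts which event**

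| Event | Rescue outcome | Endoscopic reinterventions | Primary endpoint |
|---|---|---|---|
| Coiling or surgery within 6 h, after initial and crossover treatment failed | counted | not counted | failure (no primary haemostasis) |
| Rebleed after 6 h, one repeat endoscopic haemostasis | not counted | 1 | failure (rebleed) |
| Rebleed after 6 h, repeat endoscopic haemostasis, then coiling or surgery | not counted | at least 1; the coiling or surgery is not counted | failure (rebleed) |
| Rebleed after 6 h, straight to coiling or surgery | not counted | 0 | failure (rebleed) |

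The last row is the defect. In the third row the patient is scored, but the coiling or surgery is not. A rebleed within 6 hours may also fall outside the rescue outcome, because rescue is defined by failure to reach haemostasis and not by recurrence.

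The adverse-event outcome does not close the gap. It is limited to therapy-associated events, and *Adverse event reporting and harms {22}* says: "If the event occurs due to lack of efficacy or due to the underlying disease, it shall be considered independent".

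**2. Expected rebleeds on the plan's rates**

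Inputs from *Sample size {14}*: 45 patients per arm; ET 90% primary haemostasis and 5% rebleeding; ST 72% and 16%.

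The plan's combined rate for ET is reproduced by applying rebleeding to patients with haemostasis: 0.90 × 0.95 = 0.855. The same product for ST is 0.72 × 0.84 = 0.6048, against a stated 60.1%. The difference hardly matters here: working back from 60.1% gives 45 × (0.72 − 0.601) = 5.4 ST rebleeds instead of 5.2.

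- ET: 45 × 0.90 × 0.05 = 2.03
- ST: 45 × 0.72 × 0.16 = 5.18
- Total: 7.21

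**3. Patients mis-scored**

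The documents do not give the share of rebleeds that go directly to coiling or surgery. Assumed range: 10% to 30%.

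| Assumed share | ET | ST | Total |
|---|---|---|---|
| 10% | 0.20 | 0.52 | 0.72 |
| 30% | 0.61 | 1.56 | 2.16 |

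A wider assumed range of 5% to 50% gives 7.21 × 0.05 = 0.4 to 7.21 × 0.50 = 3.6 patients.

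**4. First-line failures are not part of this number**

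Expected first-line failures are 45 × 0.28 = 12.6 (ST) and 45 × 0.10 = 4.5 (ET), but these patients go to crossover first. If the plan's first-line rates also held for crossover (an assumption), those reaching rescue would be 45 × 0.28 × 0.10 = 1.26 in ST and 45 × 0.10 × 0.28 = 1.26 in ET. That is about 1.3 per arm, with no imbalance, and rescue within 6 hours is counted.

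**The case against.** A reader might infer that these patients vanish from the results. The documents do not support that. The *Primary outcome measure* counts a rebleed to day 30 whatever treatment follows, so each of them is a primary-endpoint failure. Transfused units, hospital days, ICU days and all-cause mortality are also collected over 30 days. Only the procedure is uncounted.

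A reader might also infer that the worst courses in general score zero. They do not: anyone with another endoscopic haemostasis procedure before coiling or surgery scores at least 1.

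It is tempting to add late rescue after a failed first endoscopy. That extension is weak. Few patients should reach rescue, nothing suggests that it would be delayed beyond 6 hours, and the salvage objective in *Objectives {7}* carries no 6-hour limit. The 30-day count starts at successful endoscopic haemostasis, so a patient who never reaches it has no defined start and is not clearly scored 0.

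Nor does the gap manufacture a benefit for ET. With the same direct-to-coiling share in both arms, more is left out in ST, which works against the superiority hypothesis. The direction is open only if that share differs by arm.

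Finally, the outcome is labelled as endoscopic, agrees with its objective and is called indirect. The CRF (Additional file 1) is not shown and may record these procedures. All of this stands, and it limits the point to one secondary outcome. It does not remove the point: the measurement rule is stated explicitly and leaves these procedures out, and bringing them in after results by arm are known would be post hoc.

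**Conclusion.** The point holds in limited form. As written, coiling or surgery for a rebleed beyond the 6-hour window is in no procedure count, and a patient taken directly to either scores better on reinterventions than one controlled by a single repeat endoscopy. About 7.2 rebleeds are expected across both arms. Some 0.7 to 2.2 of these patients would be mis-scored if 10% to 30% bypass endoscopy, which is an assumed range. The number is small, but so is the number of rebleeds on which this outcome largely rests. The primary endpoint, the sample size and the other 30-day outcomes are unaffected. This is a worthwhile, inexpensive improvement to a secondary outcome and not a threat to the trial's main conclusion.

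**What to change.** Redefine the reintervention outcome as any further haemostatic intervention (endoscopic, angiographic or surgical) from the end of the index endoscopy to day 30, counted per patient and shown by type. Keep the endoscopic count as a component, so the present outcome can still be reported. Keep the 6-hour rescue outcome as a description of the index procedure, and state that coiling or surgery done as rescue soon after the index endoscopy will appear in both, so that the two are not added together. Starting the clock at the end of the index endoscopy also gives a defined start to patients who never reach endoscopic haemostasis. Align the wording in *Objectives {7}*.

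The cost is a change of outcome wording and at most one CRF field. Patient care does not change. The amendment should be made before any comparison by arm is seen.
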